## Abstract

**Introduction:**

The successful scale-up of a latent tuberculosis (TB) infection testing and treatment programme is essential to achieve TB elimination. However, poor adherence compromises its therapeutic effectiveness. Novel rifapentine-based regimens and treatment support based on behavioural science theory may improve treatment adherence and completion.

**Methods and analysis:**

A pragmatic multicentre, open-label, randomised controlled trial assessing the effect of novel short-course rifapentine-based regimens for TB prevention and additional theory-based treatment support on treatment adherence against standard-of-care. Participants aged between 16 and 65 who are eligible to start TB preventive therapy will be recruited in England. 920 participants will be randomised to one of six arms with allocation ratio of 5:5:6:6:6:6: daily isoniazid +rifampicin for 3 months (3HR), routine treatment support (control); 3HR, additional treatment support; weekly isoniazid +rifapentine for 3 months (3HP), routine treatment support; weekly 3HP, additional treatment support; daily isoniazid +rifapentine for 1 month (1HP), routine treatment support; daily 1HP, additional treatment support. Additional treatment support comprises reminders using an electronic pillbox, a short animation, and leaflets based on the perceptions and practicalities approach. The primary outcome is adequate treatment adherence, defined as taking ≥90% of allocated doses within the pre-specified treatment period, measured by electronic pillboxes. Secondary outcomes include safety and TB incidence within 12 months. We will conduct process evaluation of the trial interventions and assess intervention acceptability and fidelity and mechanisms for effect and estimate the cost-effectiveness of novel regimens. The protocol was developed with patient and public involvement, which will continue throughout the trial.

**Ethics and dissemination:**

Ethics approval has been obtained from The National Health Service Health Research Authority (20/LO/1097). All participants will be required to provide written informed consent. We will share the results in peer-reviewed journals.

**Trial registration number:**

EudraCT 2020-004444-29.

Strengths and limitations of this studyThe trial allows evaluation of both the effect of two rifapentine-based regimens compared with the standard 3-month daily rifampicin plus isoniazid, and the effect of additional treatment support compared with routine support, on latent tuberculosis infection (LTBI) treatment adherence.We will perform process evaluation of the trial interventions, including assessment of intervention acceptability and fidelity, and economic evaluation, which will provide additional evidence to inform treatment options and treatment support.The trial is powered to evaluate novel rifapentine-based regimens compared with the standard daily rifampicin plus isoniazid (3HR) and the effect of additional treatment support compared with routine support; however, it does not have sufficient power to evaluate all possible comparisons such as 3-month weekly rifapentine plus isoniazid vs 1-month daily rifapentine plus isoniazid.The trial will be conducted in England largely in migrant populations eligible for the LTBI screening programme and contacts of TB patients and thus limiting generalisability to these populations and similar settings.Adherence will be measured using electronic pillboxes in all arms while reminders will be activated only in arms with additional treatment support; however, this may impact adherence in control groups.

## Introduction

Successful implementation of screening and treatment for latent tuberculosis infection (LTBI) is critical to further reduce TB incidence globally and achieve TB elimination in low TB incidence countries.^1^ A recent call to action issued by the WHO urged for accelerating the scale-up of treatment of LTBI, particularly to mitigate the negative impact from the disruption of TB services caused by the pandemic of COVID-19.^2^

Tuberculosis (TB) in England disproportionately affects underserved communities, such as migrants and homeless people, who consequently experience higher disease burden and worse clinical outcomes. Consequently, in England, LTBI screening and treatment for high risk groups such as new migrants from high TB incidence countries is recognised as an essential strategy to achieve TB elimination.^3^ Contact tracing, including testing and treatment of LTBI among contacts, is another essential component of the TB strategy for England.^3^

Achieving optimal treatment adherence and completion is essential to ensure the efficacy of treatment for LTBI and to achieve commensurate reductions in TB incidence. Standard therapeutic options in the UK include 3 months of self-administered daily isoniazid/rifampicin and 6 months of daily isoniazid; the former regimen is often prescribed because of the availability of fixed-dose formulations and its shorter duration. While these regimen are efficacious in preventing disease, their effectiveness is limited by low treatment adherence and completion rates.^4 5^ According to data from England in migrants whose treatment outcome is known, 75% completed LTBI treatment between 2019 and 2020.^6 7^ The proportion of people who completed treatment varied by Clinical Commission Group (CCG), which was less than 70% in several CCGs.^8^

People with LTBI may need additional support to adhere to effective treatments. Treatment non-adherence can be intentional or unintentional, and is driven by a person’s motivation and ability to take medicine as prescribed, respectively.^9^ Motivation is influenced by our perceptions (eg, beliefs and preferences) and ability is determined by practical factors (eg, internal capacity and resource).^9^ These principles are operationalised as part of the perceptions and practicalities approach to supporting adherence (PAPA) and are applied in National Institute for Health and Care Excellence (NICE) guidelines.^10^ The Necessity and Concerns Framework further explains how patients’ motivation to engage with treatment is based on their perceived necessity for, and concerns about the treatment.^11^ Necessity beliefs are influenced by perceptions of the health threat (eg, LTBI) and interpretation of symptoms. The asymptomatic nature of LTBI may negatively impact necessity beliefs, and heighten treatment concerns. As such, intervention to support treatment adherence in people with LTBI will likely be more effective if they address patient beliefs and concerns around treatment, in addition to removing practical barriers.

The need to understand perceptual and practical barriers to treatment adherence, and the potential of advancing technology and drug regimens in the National Health Service (NHS) has been highlighted. Some mobile/digital technology (mHealth) has been shown to improve adherence in TB disease studies. A recent study in China found electronic reminders, using specially designed electronic medication monitors, improved treatment adherence in such TB patients, but multiple two-way daily text messaging reminders, didactic in nature, did not.^12^ Most of the evidence available is on TB disease with little research on mHealth interventions to improve LTBI treatment adherence.^13 14^ Another call to action issued by the WHO suggested TB preventive treatment programmes should consider communication technologies for medication adherence support.^15^ The evidence on mHealth interventions for LTBI treatment would contribute to their global scale-up.

Another approach to promote better treatment adherence and completion is to decrease the complexity of current LTBI regimens. A regimen that is given once weekly may result in better treatment completion than the current daily 3-month regimen. A randomised controlled trial demonstrated that a new regimen of 12 doses of weekly rifapentine and isoniazid (3HP) delivered through direct observation (ie, with patients being supervised taking each dose) is non-inferior to 9 months of daily isoniazid.^16^ Our network meta-analysis suggests that 3HP has similar efficacy to the UK standard-of-care of a 12-week, daily isoniazid/rifampicin regimen (3HR).^17^ Furthermore, a recent trial in people living with HIV (23% with LTBI as demonstrated by a positive tuberculin skin test and/or Interferon Gamma Release Assay result) demonstrated non-inferiority of daily 1-month rifapentine plus isoniazid (1HP) compared with 9 months of daily isoniazid.^18^ The 1-month regimen resulted in better adherence and fewer serious adverse events. Based on this study, and by extrapolating to HIV-negative individuals, newly published WHO guidelines recommend this regimen regardless of HIV status. However, there is no published evaluation of whether these more expensive rifapentine-based regimens lead to better treatment completion than the current daily administered UK standard-of-care. In particular, evidence is limited on the use of 3HP with patient self-administration and no study has compared its completion with 3HR.

To develop tools to reduce TB rates, we need to evaluate advancing technology and drug regimens, but also understand the barriers and enablers of adherence.^3^ To date, adherence interventions have predominantly focused on removing practical barriers to adherence (eg, reminder of shortening the drug regimen). However, such approaches applied in isolation ignore patient beliefs. LTBI is asymptomatic which means patients might have a disconnect between medical advice and their perceived need for treatment.^19^ NICE guidelines recommend a PAPA to adherence support, whereby beliefs (necessity and concerns) are elicited and addressed in addition to practical barriers.^10 11^

We previously conducted the HALT-LTBI study, a pilot study assessing the safety and treatment completion of 3HP compared with standard care.^20^ HALT-LTBI demonstrated the feasibility of recruiting LTBI patients to such a trial; no serious adverse events defined as grade 3 or more were reported, supporting the safety of rifapentine and isoniazid regimens in individuals eligible for LTBI treatment in the UK. 78% and 68% of participants completed treatment in the experimental and standard-of-care arms, respectively, but the pilot was not powered to detect differences in treatment completion. Thus, we will conduct a fully powered trial to compare treatment adherence and adverse events of novel 3HP and 1HP regimens compared with 3HR and to assess the effect of additional treatment support in participants given each regimen.

### Objectives

The primary objective of this trial is to assess the effect of novel rifapentine-based regimens (3HP or 1HP) compared with the standard 90-dose daily rifampicin plus isoniazid (3HR), and the effect of additional treatment support compared with routine support, on LTBI treatment adherence.

The secondary objectives are: (1) to evaluate the effect of LTBI treatment and additional treatment support using alternate measures of adherence outcome; and (2) to compare the frequency of adverse events while on treatment for LTBI, and development of TB within 12 months following treatment. Additionally, we will evaluate the process of delivering the adherence intervention and examine intervention fidelity and acceptability as well as the cost-effectiveness of different treatment options and/or additional treatment support.

## Method and analysis

### Trial design

A multicentre open-label randomised controlled trial with the following six parallel groups (figure 1):

**ARM 1**—Daily isoniazid +rifampicin for 3 months (3HR), routine treatment support (Standard-of-care; control arm)

**Figure 1 F1:**
[figure not shown]
Trial schema. LTBI, latent tuberculosis infection.

**ARM 2**—Daily 3HR, additional treatment support.

**ARM 3**—Weekly isoniazid +rifapentine for 3 months (3HP), routine treatment support

**ARM 4**—Weekly 3HP, additional treatment support.

**ARM 5**—Daily isoniazid +rifapentine for 1 month (1HP), routine treatment support.

**ARM 6**—Daily 1HP, additional treatment support

A factorial design was not chosen for several reasons. First, it is anticipated that there will be an interaction between type of regimen and treatment support; additional treatment support is likely to confer a smaller benefit with 3HP/1HP compared with 3HR. Second, the power to detect the effect of an intervention would be reduced if the effect of the second intervention is greater than expected.

### Study setting

The trial will recruit from secondary care sites that provide LTBI treatment in England, UK. RID-TB: Treat is part of a 5-year programme of work (RID-TB) which is funded by the National Institute for Health Research (NIHR) (RP-PG-0217-20009 https://dev.fundingawards.nihr.ac.uk/award/RP-PG-0217-20009). We expect to recruit participants from 15 care sites.

### Study population

The trial will enrol populations who are eligible for treatment for LTBI according to the national guidance. We envisage that the majority of individuals eligible for this are contacts of persons diagnosed with TB disease, and/or migrants eligible for the national LTBI screening programme.^21^ The LTBI migrant screening programme includes migrants who are aged 16 to 35 years, entered the UK from a high incidence country (≥150/100 000) or sub-Saharan Africa within the last 5 years and had been previously living in that high incidence country for 6 months or longer.^21^ Inclusion and exclusion criteria are shown in box 1.

Box 1Study inclusion and exclusion criteriaInclusion criteriaAged ≥16 years to ≤65 at screening.Latent tuberculosis infection (LTBI) diagnosis defined on the basis of all of the following:A positive result on an Interferon Gamma Release Assay, Tuberculin Skin Test or C-Tb skin test.Negative TB symptoms at screening.No signs of active TB on a chest X-ray.Eligible for LTBI treatment at TB clinics and national LTBI screening services based on National Institute for Health and Care Excellence guidelines, which means having one or more of the following :Recent infection (contact tracing).New entrants at risk (ie, those that immigrated <5 years from countries with a high incidence of TB, which is defined as ≥40 cases/100 000 population).Individuals who are assessed in the TB clinic for latent TB testing, or have been referred for treatment following testing by specialities or departments within primary or secondary care settings.Agree to LTBI treatment.Willing and able to provide written informed consent.Exclusion criteriaPatients weighing <30 kg.Need for medications that cannot be safely taken together with study drugs (eg, protease inhibitors in people living with HIV and people with refractory epilepsy taking phenytoin/carbamazepine).Any medical condition deserving priority of treatment (such as: porphyria, malabsorption syndromes, *Clostridium difficile*-associated diarrhoea and other conditions).History of sensitivity/intolerance to isoniazid or rifamycins.Individuals with documented liver disease, defined as:Liver function tests (alanine aminotransferase/aspartate aminotransferase/bilirubin) over three times upper limit of normal at baseline. This reflects normal clinical practice. For participant safety, liver function tests are carried on a regular basis. One abnormal value prevents the patient from participating on the study.Clinical diagnosis of cirrhosis (jaundice, haematemesis, ascites or previous episodes of liver encephalopathy).Hepatitis B surface antigen positive or hepatitis C virus antibody positive and deemed ineligible for LTBI treatment by the clinician.Intending to move outside of the treatment locality within 20 weeks of starting treatment.Individuals who would usually be offered LTBI treatment under Directly Observed Therapy as part of enhanced case management in complex cases such as those from under-served groups (such as people who are homeless, misuse substances, have been in prison or who are vulnerable migrants).Use of another experimental investigational medicinal product that is likely to interfere with the study medication within 3 months of study enrolment.Women who are breast feeding, pregnant or of childbearing potential who do not agree to use an effective method of contraception from the time consent is signed until 4 weeks after treatment discontinuation or completion. Males whose partners are of childbearing potential must also agree to use an effective method of contraception.Women of childbearing potential without a negative urine pregnancy test within 7 days prior to being registered for trial treatment.

Participants will be identified from secondary care settings in the UK where persons eligible for treatment for LTBI are managed. Participants will be recruited individually, but if any participants share a household, they will be allocated to the same arm as the first person recruited from that household (effectively resulting in randomisation by household).

Non-English speakers will not be excluded from the trial. We will translate patient-facing materials and use interpreters to support non-English-speaking participants.

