### Sample size

The six-arm design allows evaluation of:

The effect of the novel treatment regimens (3HP and 1HP) vs standard-of-care regimen (3HR), under routine treatment support.The effect of additional treatment support vs routine treatment support for each individual regimen.

A total of 920 participants are to be recruited. This provides 80% power for each of the following comparisons:

Arm 3 vs Arm 1—that is, 3HP+routine treatment support vs 3HR+routine treatment support.Arm 5 vs Arm 1—that is, 1HP+routine treatment support vs 3 HR+routine treatment support.Arm 2 vs Arm 1—that is, 3HR+additional treatment support vs 3HR+routine treatment support.Arm 4 vs Arm 3—that is, 3HP+additional treatment support vs 3HP+routine treatment support.Arm 6 vs Arm 5—that is, 1HP+additional treatment support vs 1HP+routine treatment support.

The power calculations assume the following:

70% adherence rate in Arm 1.3HP and 1HP improve adherence rate by 15% (absolute difference) compared with 3HR, respectively, with routine treatment support.^18 23 24^Compared with routine treatment support, additional treatment support improves adherence rate by 15% for 3HR, and 10% for 3HP and 1HP, respectively.^12^Two-sided alpha 5% (see below for type I error considerations).Average number of participants enrolled per household is 2, taking into account the average household size in UK.^25^Intra-class correlation within a household is 0.1

The 70% adherence rate assumed for Arm 1 is based on the 77% LTBI treatment completion rate reported from the Public Health England LTBI testing and treatment database for 2018.^26^

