### Blinding

This is an open-label trial. Blinding of participants and care providers to the allocation group is not relevant since the primary objective of this trial is to examine the effect of shorter or weekly regimens and additional treatment support on treatment adherence.

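### Later household members can know their arm before they consent, so allocation concealment is assured only for the first member of each household

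*Protocol article*

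**What the plan says.** The Study population section of the protocol article sets the rule. Recruitment is by individual, yet for people living at one address the section provides that "they will be allocated to the same arm as the first person recruited from that household". It describes the result as, in effect, randomisation by household.

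Other sections bear on how this works:

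- **Blinding:** "This is an open-label trial".
- **Randomisation and allocation:** central computerised minimisation with a random element, balanced on centre and TB exposure risk group.
- **Box 1:** agreement to LTBI treatment and written consent are inclusion criteria for each person.
- **Screening, randomisation and baseline assessment:** consent, screening and randomisation are described participant by participant. No step covers other members of the household.
- **Sample size:** "Average number of participants enrolled per household is 2, taking into account the average household size in UK", and "Intra-class correlation within a household is 0.1".
- **Statistical methods:** the primary analysis takes all randomised participants, apart from those found to have had TB disease at baseline, in a log-binomial mixed model that allows for correlation within households. The sensitivity analyses concern loss to follow-up. The supplementary ones vary the adherence threshold, the time frame and the analysis population.

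**The concern.** Once the first member is randomised, the arm of anyone who joins later from that household is fixed and visible. A later member decides whether to consent when the choice may already be a known one: 90 daily, 12 weekly or 28 daily doses, with or without reminders. Staff decide whether to approach that person in the same position. This is the recruitment bias familiar from cluster trials in which individuals are enrolled after the cluster has been allocated.

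The outcome makes it matter here. The Introduction attributes adherence to motivation, including beliefs and preferences, and to practical ability. Willingness to join a known regimen plausibly draws on the same factors. If later members join selectively and the selection differs by arm, the arms differ in underlying adherence before any treatment effect. All three primary comparisons could be affected, including (c), because the support package is visible too. A household random effect deals with dependence between members; it does not make the later members of two arms comparable.

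**Working it through.** **1. The plan's own figure.** Inputs from Sample size and the Abstract: 70% adherence in Arm 1; 85% for 3HP and 1HP with routine support and for 3HR with additional support; 95% for 3HP and 1HP with additional support; two-sided alpha 5%; 80% power; 2 per household; intra-class correlation 0.1; ratio 5:5:6:6:6:6.

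- Design effect: 1 + (2 − 1) × 0.1 = 1.10.
- 70% v 85% (pooled variance, no continuity correction): 121 × 1.10 = 133.1 per arm.
- 85% v 95%: 141 × 1.10 = 155.1 per arm.
- Total at the stated ratio: max(133.1/5, 155.1/6) × 34 = 26.62 × 34 = 905, within 2% of the stated 920.
- Power at 920 is 84% (Arms 3 v 1 and 5 v 1), 81% (2 v 1) and 82% (4 v 3 and 6 v 5).

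The sample size therefore reproduces, with 2 per household as one of its inputs.

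**2. Share who enter after the household's arm is fixed.** With mean m enrolled per household there are 920/m households, hence 920/m first members. Later members make up 1 − 1/m of the total, whatever the distribution of household sizes.

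| Mean per household | Later members | Share |
|---|---|---|
| 1.1 | 84 | 9% |
| 1.25 | 184 | 20% |
| 1.5 | 307 | 33% |
| 2 (planning value) | 460 | 50% |

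At m = 2 this is about 68 of 135 in Arms 1 and 2, and 81 of 162 in each of the others. Later members who consent before the first is randomised remain concealed, so each row is an upper figure for its mean.

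**3. Illustration: declining Arm 1 (assumed inputs).** Take 2 as the number per household before anyone declines. Let a fraction d of later members decline Arm 1, with adherence p among decliners and 70% overall. The later members who join have adherence (0.70 − d·p)/(1 − d), so Arm 1 adherence is (0.70 + 0.70 − d·p)/(2 − d).

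| d | p = 0.5 | p = 0.4 |
|---|---|---|
| 0.1 | 1.35/1.9 = 0.711 (+1.1 points) | 1.36/1.9 = 0.716 (+1.6) |
| 0.2 | 1.30/1.8 = 0.722 (+2.2) | 1.32/1.8 = 0.733 (+3.3) |
| 0.3 | 1.25/1.7 = 0.735 (+3.5) | 1.28/1.7 = 0.753 (+5.3) |

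Arm 1 rises by 1.1 to 5.3 points. With Arms 3 and 5 unaffected, the planned 15-point difference in (a) and (b) shrinks to between 13.9 and 9.7 points, towards the null. The effect on (c) depends on whether Arm 2, which has the same drugs, loses the same people.

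**4. Illustration: no true effect (assumed inputs).** If selection alone makes later members of Arms 3 and 1 differ by 5 or 10 points, and later members are half of each arm, the bias is 2.5 or 5 points. The standard error at 70% adherence, with arm sizes divided by 1.10, is √(0.21 × (1/123.0 + 1/147.6)) = 0.056. Two-sided type I error then becomes about 7% or 15% in place of 5%.

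**5. Power with first members only.** At m = 2, halving each arm and dropping the design effect gives about 60% (3 v 1 and 5 v 1), 55% (2 v 1) and 57% (4 v 3 and 6 v 5).

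**The case against.** **Half is a planning figure.** The mean of 2 takes account of UK household size and serves the design effect. Only members aged 16 to 65 who test positive, are otherwise eligible and consent can enrol, so the true mean may be well below 2. This stands: a reader might infer that half the participants enter unconcealed, and the document supports only up to half under that assumption.

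**Knowledge of the arm is inferred.** Nowhere does the article say that later members are told the arm before consent. Screening may also fall on an earlier day than randomisation, so joint consent is possible. Both are true, but joint consent is not required, and open-label treatment within a home makes knowledge of the arm easy.

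**Direction and size are unknown.** 3HR is often prescribed outside the trial, so declining Arm 1 would probably bring the same drugs. Extra joining in the rifapentine arms may be likelier than refusal of Arm 1. This also stands: a reader might take the illustration as a prediction of bias towards the null, but it is one scenario resting on assumed inputs. It also treats 2 as a count before declining, whereas the article's 2 is the number enrolled.

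**The text is abridged.** The article condenses protocol V.3.0, which is not shown and may describe a household procedure, and extra sensitivity analyses often sit in an analysis plan. A reader should therefore not infer that the trial has no safeguard at all. The point rests on the rule that the article does state.

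**Household allocation has good reasons.** Leaflets, animation and regimens could otherwise be mixed within one home. Agreed; the rule itself need not change.

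**Conclusion.** The point holds as a risk created by a stated rule. Individual recruitment, inheritance of the first member's arm and open-label treatment together mean that concealment is assured only for first members. Up to 460 of 920 participants could be exposed if 2 are enrolled per household, about 9% to 33% if the mean is 1.1 to 1.5, and fewer where members consent together beforehand.

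Any of the primary comparisons could be biased, and the random effect for household does not correct it. The document cannot settle direction or magnitude; the 1.1 to 5.3 points for Arm 1, and the type I error of 7% or 15%, depend on the assumed inputs shown. The point does not show that the trial's results would be biased. It is a safeguard worth adding, inexpensive because the Trial status section says recruitment had not begun.

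**What to change.** Keep household allocation and add three things.

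1. Where two or more potentially eligible members of a household are known, obtain consent and confirm eligibility for all of them before the household is randomised.
2. Record each participant's order of recruitment within the household, and whether consent came before the household's allocation was known. This has to be captured prospectively.
3. Pre-specify, for each primary comparison, a sensitivity analysis restricted to members who consented before that point, and compare the number and baseline features of later members by arm.

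The cost is a randomisation instruction, two database items and one further analysis, with a short delay for some households. If the restricted set comes down to first members only, power is about 55% to 60% at 2 per household. The analysis therefore supports the primary one and does not replace it; members who consented jointly would add to its precision.
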